### Protection of privacy, ethical issues and expected adverse effects

The research protocol of this study was approved by the Committee of Medical Ethics of the Ghent University Hospital (Belgian registration number: B670201731996) and registered as a clinical trial at https://register.clinicaltrials.gov (ID number: NCT03274271). Participants will provide web-based informed consent regarding the study measures and log data of the website and app before enrolling in the study. They will be informed about the purpose and the design of the study, the potential benefits and risks, the voluntary basis of the study and how their personal information will be processed. Personal information will be coded and password-protected. Only researchers that are part of the research team will have access to the data. No incentive will be provided to the participants. It is expected that they will experience health benefits from an increase in PA or a decrease in SB. However, in the unlikely event that users may experience adverse effects, such as severe joint or muscle pain, participants will be encouraged to report adverse effects and will be advised to consult a physician in that case. Precautions to prevent adverse effects have been made by screening for health problems in the recruitment phase (see ‘Participants’).

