### Measurements

To answer our research questions, outcomes will be measured at five time points: 1 week before the intervention (PRE), immediately after session 1 (T1), immediately after session 3 (T2), maximum 1 week after the intervention (POST) and 1 month after the intervention (FU). Figure 3 shows which variables will be measured at each time point.

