#### Dose delivered

Dose delivered, or completeness, is the quantification of components of the website that were actually delivered in comparison to the components available. This will be measured by keeping track of the users’ website and app log data and counting how many online sessions they initiated and completed. We will keep track of how long users spend time on the website and app using the different components, how long it takes them to log back in and complete the intervention, how many times they have to be reminded for logging in again, if users complete optional components (such as the quizzes), and how many times they adapt their plan. Furthermore, at three different points in time (after session 3, post-intervention and follow-up intervention) users will rate how often they use the app (i.e. never, less than 1 day/week, 1 to 2 days/week, 3 to 4 days/week, 5 to 6 days/week, daily).

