#### Context

Context discusses possible influences of the environment on intervention implementation and outcomes. The most important influence of context on the implementation of the intervention will be assessed via the short version of the ALPHA questionnaire [66], as mentioned above, and the following question: ‘Did physical or emotional problems prevent you from being more physically active/less sedentary?’

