### Data collection procedures

The flowchart of the data collection procedure can be found in Fig. 4. Data collection started in March 2018 and is aimed to finish in April 2019. Participants will be recruited in the city library of Ghent (i.e. ‘De Krook’), in city halls and shopping malls. If a participant is willing to co-operate in the study, they will be offered a tablet and the pre-test measurement will take place. The participant will provide informed consent, choose a behaviour (PA or SB) and complete the questionnaires (see Fig. 3) via an online survey tool (https://www.limesurvey.org/) [72]. Subsequently, researchers will provide instructions on how to download the app. If the participant does not have sufficient time to fill out the questionnaire, they will receive a folder with a link and login code to start/complete the pre-test measurement at home. After completion of the pre-test measurement, the participant will be allocated to one of the eight groups, and will receive an email with the web-link to the appropriate version of the intervention. MyPlan 2.0 and its different conditions can only be accessed via the link sent by the researcher and, later on, via the provided email address of the participant. Participants have no access to the other experimental conditions of MyPlan 2.0. One week after each intervention session, an automatic email to encourage people to start with the following session will be sent. If participants take longer than expected to a complete session, several actions will be taken. Participants who do not start or complete a session after 1 week will be sent an email reminder. When there is no reaction after 2 weeks, participants will receive a telephone call from the researcher. When there is no reaction after 3 weeks, the participant will be considered as a drop-out.

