**Fig. 4 Fig4:**
[figure not shown]
Flowchart of data collection

Maximum 1 week after completing the five online intervention sessions, participants will receive an email with the link to the post-intervention measures about PA, SB and determinants of behaviour change (see Fig. 3). The post-intervention measures will also include questions about app usage, intervention appreciation and attrition-related factors, necessary for the process evaluation. One month after intervention completion, participants will again receive an email with a link to the follow-up measures (see Fig. 3).

In order to be able to conduct mediation and moderator analyses and track the change in the determinants of behaviour change, participants will complete the item set regarding the determinants after session 1 and session 3. The link and login will be integrated in the email for sessions 1 and 3.

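### Adverse effects are described as spontaneously reported, with no uniform question at the questionnaires all eight groups already complete, so counts are likely too low and a low count cannot be interpreted

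*Protocol article*

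**What the plan says.** The section on privacy, ethical issues and expected adverse effects is the only place in the protocol article that says how adverse effects are collected. It names the kind of harm expected, "in the unlikely event that users may experience adverse effects, such as severe joint or muscle pain", and states that "participants will be encouraged to report adverse effects and will be advised to consult a physician in that case". Otherwise risk is handled at entry: anyone endorsing an item of the readiness questionnaire is excluded (Participants).

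All groups have scheduled questionnaires. The Measurements section lists five time points: pre-test, after session 1 (T1), after session 3 (T2), post-test (POST) and one-month follow-up (FU). Under Data collection procedures, "participants will complete the item set regarding the determinants after session 1 and session 3", and "The post-intervention measures will also include questions about app usage, intervention appreciation and attrition-related factors, necessary for the process evaluation". Under Dose delivered, "at three different points in time (after session 3, post-intervention and follow-up intervention) users will rate how often they use the app".

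Two other prompts touch on health. Under Context, participants are asked "Did physical or emotional problems prevent you from being more physically active/less sedentary"; the text gives no time point for this. Under Dose received, people who discontinue are telephoned, asked in their own words why they stopped, and then asked to rate listed reasons, one of which covers medical and emotional difficulties.

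**The concern.** Spontaneous reporting by people using a programme on their own at home usually misses events. Here a specific harm is foreseen and structured online questionnaires already reach every group, yet none of the questionnaire content described asks whether becoming more active or sitting less led to pain, injury or another health problem.

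The trial is meant to guide which behaviour-change techniques to keep or remove. If the publication says that few or no adverse effects occurred, a reader may take that as evidence that the recommended version is safe. With spontaneous reporting alone, that sentence would be equally compatible with nobody having been asked. Participants with a problem may also go unnoticed while the trial runs.

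**Working it through.** The document gives no adverse-effect rate, count or reporting probability, so there is no figure of its own to reproduce. The check sets the described prompts side by side; the arithmetic after that is illustrative where marked.

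**1. Who is asked what**

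| Prompt | Who is reached | What it captures |
|---|---|---|
| Encouragement to report (ethics section) | Anyone who takes the initiative | Adverse effects, if volunteered |
| Context question | Participants generally; timing not given in the text | Whether a physical or emotional problem was a barrier |
| Drop-out call (Dose received) | Only those who discontinue | Whether a medical or emotional problem was a reason to stop |
| Printed questionnaire items (Tables 2 and 3) | Questionnaire respondents | Appreciation and attrition factors; no harm item |

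The Context question runs in the other direction from a harm question. Someone who develops knee pain but keeps walking can truthfully answer no; someone with low mood unrelated to the study can truthfully answer yes. The drop-out call could reveal harm, but not in people who continue. Neither measures harm uniformly.

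**2. Length of the period concerned**

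Sessions are weekly, and "When there is no reaction after 3 weeks, the participant will be considered as a drop-out". There are 4 intervals between sessions 1 and 5.
- Shortest: 4 × 1 = 4 weeks.
- Longest, if the 3 weeks run from the previous session: 4 × 3 = 12 weeks.
- Longest, if they run from the due date: 4 × (1 + 3) = 16 weeks.

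One further month to follow-up is added. The upper values need near-maximal lateness at every session.

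**3. Under-counting (assumed rates)**

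Recorded events = n × true risk × probability of reporting. Each technique is present in 4 groups of 60, so n = 240 per level.

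| Assumed true risk | True events per 240 | Recorded at 20% reporting | Recorded at 80% reporting |
|---|---|---|---|
| 2% | 4.8 | 1.0 | 3.8 |
| 5% | 12 | 2.4 | 9.6 |
| 10% | 24 | 4.8 | 19.2 |

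For the whole sample at 5%: 480 × 0.05 = 24 events; at 20-50% reporting, about 5 to 12 are seen. Any reporting probability below 100% gives an under-count; its size is unknown.

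**4. Comparability between technique levels**

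With equal true risk, the apparent risk ratio equals the ratio of the reporting probabilities.
- Equal reporting: ratio 1.0. Counts are too low but still comparable.
- Assumed 30% v 45%: 0.45 / 0.30 = 1.5. At an assumed 10% true risk and 240 per level, the chance of a spurious significant difference is about 14%.
- Assumed 30% v 60%: 0.60 / 0.30 = 2.0; that chance is about 35%.

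Distortion therefore requires reporting that differs by group, which the document does not establish.

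**5. What zero reports would mean**

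If everyone were asked and nobody reported an event, the one-sided 95% upper bound is 1 − 0.05^(1/n).
- n = 240: 1.24%.
- n = 130 (half of the 260 that the sample-size paragraph requires): 2.28%. This bound would describe only people who stayed in the study.

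With spontaneous reporting, no such bound can be stated.

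**The case against.** The strongest objection is that absence is not proven. The figure listing the variables at each time point is not visible, and a condensed article may leave safety procedures to a fuller document. This stands as a limit: the figure could list an item. It does not remove the point, because the article is not silent. It states a method, and that method is spontaneous reporting.

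A reader might infer that harm surfaces only if a participant volunteers it. That goes too far. The drop-out call solicits medical reasons for stopping, and the Context question solicits physical problems. These are partial prompts, not uniform harm measurement.

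A reader might also infer that counts will not be comparable between techniques. The documents do not support this. Contact does differ: self-monitoring users get an evening prompt, and the researcher is unblinded after assignment. But that prompt asks for a score of success with the plan and is not described as a reporting channel; action-planning users also receive app reminders; and emails, reminders and calls follow one rule for all groups, with calls triggered by non-response rather than by technique. The statistical analysis section plans no harm comparison.

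Finally, the risk is modest: the sample is screened, goals are self-formulated, adverse effects are called unlikely, and limiting questionnaire burden is a deliberate choice against attrition. This bears on severity. One item is nevertheless small beside the 32-item determinant set.

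**Conclusion.** The concern holds in limited form. As described, adverse effects as such are spontaneously reported, with no uniform question at questionnaires that reach all eight groups. Counts are likely too low, and a low count would not be interpretable as low harm. They could also differ between groups if reporting varies with contact, but that is a possibility, not something the document shows.

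The direction of the under-count rests on reporting being incomplete. Its size rests on assumed risks and reporting probabilities and should not be quoted as an estimate. The conclusion also assumes that the unseen schedule figure lists no harm item. No planned efficacy estimate or test is affected. This is an inexpensive improvement to harm ascertainment that should be made.

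**What to change.** - Keep spontaneous reporting.
- Add one item, worded identically in all eight groups, to the existing T2, POST and FU questionnaires: since the last questionnaire, has the participant had pain, an injury or another health problem that they attribute to being more active or sitting less? T1 falls immediately after the first session, too early to be informative.
- Ask the same item in the existing drop-out call, adapted only in its recall period. Without this, people who stop because of harm are missed.
- Report the answers descriptively by technique present v absent, separately from spontaneous reports, with the number asked and the number answering.
- Where participants are already past these points, state that their adverse effects were spontaneously reported and that no harm rate or between-technique conclusion will be drawn for them.

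Cost: one item in online questionnaires and a call that already exist, a short amendment and one descriptive table. Randomisation, sample size and the primary analysis do not change. The downsides are slightly more burden and partial data, since the trial began in March 2018 and aims to finish in April 2019.

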## Discussion

There is a need for effective e- and m-health interventions that enhance behaviour change. Additionally, e- and m-health interventions need to be relevant, time-efficient and engaging. This study may contribute to a further understanding of how, why and for whom interventions work. By investigating the role of various behaviour-change techniques and determinants of behaviour change, we will be able to provide guidance for the development of future e- and m-health interventions. One of the strengths of this study is its experimental and longitudinal design, allowing us to isolate the effects of the separate behaviour-change techniques. To our knowledge, the influence of behaviour-change techniques has only been investigated as a combined effect or in a non-experimental way [53, 82, 83] and many authors in the field refer to the need for an experimental design [33–35]. Another strength of the study is the fact that not only PA and SB are measured via self-reports, but also a range of determinants is measured at different points in time, i.e. pre, post, at follow-up and during the intervention. This allows a thorough analysis of the processes of behaviour change that interventions can target. The results of such analysis can inform future interventions on how to tailor behaviour-change techniques to different participants in various phases of behaviour change. This study should provide a large and rich dataset to explore these research questions in detail. However, the study also has some limitations. First, PA and SB are measured by self-report questionnaires (IPAQ or SIT-Q-7d), which may lead to response and recall biases [84]. Future research may consider the use of objective measures of PA and SB. Second, to lower the burden for participants and thus preventing attrition, each determinant of behaviour change will be measured via only three items, which can compromise the reliability and validity of the measurement. However, the items that are included were iteratively constructed and validated by experts in health psychology. Third, the size of the groups will not allow us to draw conclusions about the three-way interactions. However, we are more interested in the main effects and the two-way interaction effects. Fourth, because participants can freely choose either to improve their PA or to reduce their SB, we cannot ensure that both versions of the programme will have the same number of participants. Lastly, due to attrition, it is possible that the sample size between groups will differ. Therefore, it will be important to focus on keeping the participants in the study via the use of email reminders and telephone calls.

## Trial status

The final website and app have been developed. The factorial randomised controlled trial started in March 2018 and we aim to finish in April 2019 as participants can start the study at different moments. The authors will report important protocol modifications at clinicaltrials.gov.

## Data Availability

Not applicable.

## Abbreviations

ALPHA: Instruments for Assessing Levels of Physical Activity and fitness
FU: Follow-up, 1 month after the intervention
IPAQ: International Physical Activity Questionnaire
MVPA: Moderate to vigorous physical activity
PA: Physical activity
PAR-Q: Physical Activity Readiness Questionnaire
POST: Post-test, after the intervention
PRE: Pre-test, 1 week before the intervention
SB: Sedentary behaviour
SIT-Q-7d: Last 7-days Sedentary Behaviour Questionnaire
T1: Time point 1, after session 1
T2: Time point 2, after session 3
